#### Clinical Routine and Study Flow

Figure 4 illustrates the current diagnostic work-up for pulmonary embolism in the diagnostic strategy for CTEPH, the additionally conducted study procedures and the path of verification and diagnostic decision in the CHANGE-MRI trial.

**Figure 4 F4:**
[figure not shown]
Integration of the MRI scan in the clinical workflow in the CHANGE-MRI study.

### In-place Assessment

In this study at each site standard operating procedures are implemented with the aim that the in-place assessment of SPECT (following the clinical routine) and MRI are performed and evaluated independently by two different readers from different teams. The respective diagnoses are termed in-place assessments and are used for secondary analyses. Both readers are aware of the medical history of the patient under investigation but are not allowed to know the diagnosis made with the aid of the other test, as the reference test is already clinically established and, as such, bares some information. In accordance, the system for electronic Case Report Forms is set up in a way that each reader‘s access is restricted to the respective imaging method.

If required by the treating pneumologist, CPA/CTPA is performed and evaluated at the study site, as well.

### Blinded-Reader Assessment

A centrally organized blinded reader assessment of SPECT and functional MRI will be implemented to ensure that no information carry-over occurs from clinical SPECT diagnosis to the functional MRI diagnosis or vice versa. Therefore, this blinded reader assessments will be used for the primary analysis. All SPECTs and functional MRIs will undergo a blinded read where independent expert readers are randomly selected for each center and each imaging method from one of the other centers. The second reader is not aware of the findings from the initial in-place read and the respective other imaging method but has access to the patient‘s clinical information used in the in-place SPECT read. Additional to ensuring a truly blinded assessment of the imaging methods, the standardized blinded reader assessment allows assessing inter-rater agreement and context sensitivity of the diagnostic evaluations. If there is a discrepancy between the in-place read and the second reader, a final consensus read will be performed by a third expert reader.

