### Outcome Measures

SPECT and MRI will be compared based on a standardized blinded reader assessment of the imaging methods as well as based on the in-place assessments as part of a workflow incorporated into the clinical routine. To definitely exclude information carry-over in the primary analysis, the following co-primary endpoints are calculated based on the standardized blinded reader assessment:

- The proportion of patients with positive MRI in the group of patients who have a positive SPECT diagnosis for chronic pulmonary embolism and who are positive in the gold standard- The proportion of patients with positive MRI in the group of patients with negative SPECT who are negative in the gold standard.

The co-primary endpoint will also be analyzed based on the in-place assessment and results will be compared to assess the inter-rater agreement and context sensitivity of the diagnostic evaluations and to evaluate the external validity and generalizability of the primary results. Additional secondary endpoints based on the in-place assessment and the blinded-reader assessment include the diagnostic measures sensitivity, specificity, positive and negative predictive values of MRI and SPECT as compared to the defined gold standard. To assess additional benefit of the MRI compared to the SPECT, the proportion of patients with positive MRI in the group of patients who have a negative SPECT, but are positive in the gold standard, and the proportion of patients with negative MRI in patients who are SPECT positive, but have a negative gold standard, will be evaluated.

To assess the safety, the occurrence of allergic reactions or other adverse events, non-completed procedures, reasons for non-completion, non-diagnostic procedures, reasons for non-diagnostic, and the quality of the images will be evaluated for both imaging techniques.

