# *Row percentages*.

### Statistical Analysis

The primary analysis will be performed in a modified intention-to-treat population, i.e., patients will only be excluded from the analysis, if for all three diagnostic tests no assessment (neither in-place nor blinded) is available and no further follow-up data on the clinical diagnosis after 6–12 months is available. The overall two-sided type-I-error probability is set to 5%. Point estimates and 95% Wilson confidence intervals will be calculated for both co-primary endpoints based on the blinded reader assessments. Since both endpoints are evaluated co-primarily, no correction for the overall type-I-error probability is necessary.

Imputation of missing values is conducted dependent on whether any assessments of SPECT, MRI or CPA/CTPA images and clinical follow up diagnosis are available or not. If either in-place or blinded reader assessments are available, missing values of MRI or SPECT will preferably be replaced by the results of the respective available assessments. In the case of missing values because the test has not been performed at all or neither in-place nor blinded assessment are available, missing values of MRI or SPECT will be replaced using a conservative strategy in favor of SPECT, where missing information for the experimental functional MRI in all instances is counted such that sensitivity and specificity are diminished as compared with SPECT.

If missing values occur for all three diagnostics MRI, VQ-SPECT, and gold standard (e.g., because the patient decided against the study directly after written informed consent) and no further follow-up information is available for the patient, the patient is omitted from the analysis population and no imputation will be performed.

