## Discussion

In this study also Q-SPECT/CT is accepted as an approximation of the VQ-SPECT as reference test, reflecting current clinical practice and real-world test performance, although not in compliance with the current ESC/ERS guidelines (8, 17). This omission of V-SPECT will affect in particular specificity of the reference test in cases of Q-SPECT/CT, for CT cannot be regarded as a fully equivalent substitute for V SPECT.

For primary evaluation, the blinded reader assessment of SPECT and MRI are used to ensure the independency of the assessments and maximize internal validity. On the other hand, external validity of the results might be reduced by the standardized blinded assessment, which does not necessarily reproduce the clinical field of application completely. Consequently, for analyzing the external validity and generalizability of the results based on the primary blinded assessment, the in-place assessments of SPECT and MRI are used as secondary endpoints. While the independence of these assessments cannot be guaranteed, the clinical setting is well represented.

To avoid an increased radiation burden, in this trial the current gold-standard instrument CPA/CTPA is routinely only applied in SPECT-positive patients, which might induce differential verification bias (6, 19, 20). To mitigate this limitation, the follow-up information up to 1 year after study inclusion will be included into the final diagnosis of PE by correcting negative cases, which subsequently are identified as positive in the follow-up period or (although less probable) correcting positive cases, which subsequently are identified as negative.

Ethics votes from the Institutional Review Boards at all participating centers were obtained. The CHANGE-MRI study is designed so that no extra radiation in addition to the clinically indicated radiation-based imaging tests is applied to the study participants. Thus, approval by the Federal Office for radiation protection (Bundesamt für Strahlenschutz) was not required.

This study is conducted in compliance with the Declaration of Helsinki, ICH-E6-guidance, and for design issues regarding diagnostic validation studies, and the EMA Guideline on the Clinical Evaluation of Diagnostic Agents.

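### The in-place read, whose independence is not assured, can enter the primary analysis through the replacement rule and the third-reader trigger, although that analysis is said to exclude carry-over

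*Protocol article*

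**What the plan says.** Outcome Measures gives the reason for the central read: "To definitely exclude information carry-over in the primary analysis, the following co-primary endpoints are calculated based on the standardized blinded reader assessment". In-place Assessment assigns the local reads to secondary analyses.

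Three rules bear on whether that separation holds.

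- **Blinded-Reader Assessment** states the second reader's blinding: "The second reader is not aware of the findings from the initial in-place read and the respective other imaging method". It then adds: "If there is a discrepancy between the in-place read and the second reader, a final consensus read will be performed by a third expert reader". No blinding is stated for the third reader, and the article does not say outright whether the second read or the consensus result is the primary value.
- **Statistical Analysis** says that where either kind of read exists, "missing values of MRI or SPECT will preferably be replaced by the results of the respective available assessments". The conservative rule against MRI applies only when the test was not done or neither read exists.
- **In-place Assessment** intends the local readers to be blind to the other test: they "are not allowed to know the diagnosis made with the aid of the other test", come from different teams and have restricted eCRF access. The Discussion nevertheless concedes: "While the independence of these assessments cannot be guaranteed, the clinical setting is well represented". The in-place sensitivity analysis treats blinding as intact only where the MRI diagnosis was entered before the SPECT assessment.

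**The concern.** The central read exists to keep the SPECT result out of the MRI result and the reverse. The in-place read is the one the authors cannot vouch for, yet it supplies the primary value when a blinded read is missing. On the natural reading of the consensus rule, it also selects which blinded results may be overturned: a second-reader error that matches the in-place read stands, and one that differs from it is reopened.

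If in-place MRI reads lean towards SPECT, MRI positivity rises among patients positive on SPECT and gold standard, and falls among those negative on both. Both shifts are towards success.

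A separate effect needs no carry-over. If the third read is final, the analysed value is in effect a majority of three reads, which is more accurate than one read unless the readers share their errors. The choice of primary value therefore changes what each co-primary proportion measures.

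**Working it through.** **1. The plan's own figures.** Inputs from Sample Size and Table 2: one-sided 2.5%, power 80%, 95% against 98%, 10% against 6%. The formula is n = [1.960·√(p0(1−p0)) + 0.842·√(p1(1−p1))]² / (p1−p0)².

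- Endpoint 1: (0.4272 + 0.1178)² / 0.03² = 330.02, rounded up to 331, as stated.
- Endpoint 2: (0.5880 + 0.1999)² / 0.04² = 387.96, rounded up to 388, as stated.
- Totals: 331/0.58 = 571, as stated; 388/0.36 = 1078, against the stated 1080.

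With a 95% Wilson interval, success needs at least 323 of 331 and at most 27 of 388. For a single read exactly at the limits, the exact chance of passing is 1.4% and 2.4%.

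**2. Replacement rule (carry-over).** Let a share m of blinded reads be replaced, and let a share c of in-place MRI reads copy SPECT, which is right in both endpoint cells. Other reads sit at the limits. Then

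- endpoint 1 = (1−m)·0.95 + m·[c + (1−c)·0.95]
- endpoint 2 = (1−m)·0.10 + m·(1−c)·0.10

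| m | c | Endpoint 1 | Endpoint 2 |
|---|---|---|---|
| 5% | 50% | 95.1% | 9.75% |
| 10% | 100% | 95.5% | 9.0% |

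The values of m and c are assumptions.

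**3. Consensus rule, no carry-over.** Take the final value as the second read b if it agrees with the in-place read i, otherwise the third read t: P = b·i + [b(1−i) + (1−b)i]·t.

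- Independent errors, all reads at 95%: 0.9025 + 0.095 × 0.95 = 0.9928.
- Independent errors, all reads at a 10% false-positive rate: 0.01 + 0.18 × 0.10 = 0.028.

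Now let a share s of each reader's error be common to all three. For single-read error e, the common part is se, the residual error is r = (e−se)/(1−se), and the consensus error is se + (1−se)(3r²−2r³). Example with e = 0.05 and s = 0.5: r = 0.025/0.975 = 0.0256, and the consensus error is 0.025 + 0.975 × 0.00194 = 0.0269.

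Joint success is the product of the two exact binomial chances under the Wilson rule. It is shown at the required subgroup sizes and at those expected from 1080 patients (1080 × 0.576 = 622; 1080 × 0.36 = 389).

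| Errors shared | Endpoint 1 | Endpoint 2 | Joint success, 331/388 | Joint success, 622/389 |
|---|---|---|---|---|
| 0% | 99.3% | 2.8% | >99% | >99% |
| 50% | 97.3% | 5.8% | 41% | 72% |
| 80% | 96.0% | 8.1% | 2% | 4% |
| 100% | 95.0% | 10.0% | 0.03% | 0.05% |

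A model with a common inter-reader correlation agrees in direction: 96.9%/6.8% at 0.25 and 95.7%/8.8% at 0.5.

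**4. Carry-over through the consensus rule.** Keep second and third reads at the limits with independent errors, and let a share c of in-place reads copy SPECT.

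| c | Endpoint 1 | Endpoint 2 |
|---|---|---|
| 0 | 99.28% | 2.8% |
| 10% | 99.32% | 2.6% |
| 50% | 99.5% | 1.9% |
| 100% | 99.75% | 1.0% |

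Most of the movement away from 95%/10% comes from adding reads, and little from carry-over.

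**The case against.** Several points against the concern stand.

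- **The in-place read is not unblinded.** A reader might infer that it is. In-place Assessment and Methods Against Bias both set out to keep it blind, by rule, by site procedures and by eCRF access. The text supports only that its independence is not assured.
- **The consensus is not stated to be the primary value.** Calling the third read final points that way, but the article says throughout that the blinded assessment is analysed, and the full protocol may settle it.
- **Single-read accuracy is not a stated target.** A reader might infer that the plan overstates it. The hypotheses speak only of MRI being positive, and adjudicating discordant reads is a legitimate design.
- **The high success rates depend on an assumption.** The 72% in the working needs half of all errors to be shared; at 80% shared it is 4%. Hard images plausibly produce shared errors.
- **Part of the problem is already limited.** All scans are meant to have a blinded read, so replacement should be uncommon. When the two reads agree, the blinded value is unchanged. The per-protocol analysis on the blinded read may drop replaced values.

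These points reduce the size and certainty of the effect. They leave the contradiction in place: the replacement rule is explicit, carries no condition on the order of data entry, and sits in the primary analysis. The per-protocol analysis is only a sensitivity analysis and leaves the consensus trigger untouched. No analysis of the second read alone is described.

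**Conclusion.** The point holds in a limited form. Followed as written, the replacement rule breaks the assurance that carry-over is definitely excluded. The consensus rule does so too if, as the wording suggests, the third read supplies the primary value.

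The bias favours MRI on both endpoints, given that in-place contamination pulls MRI towards SPECT and that single reads are right more often than wrong. Its carry-over part is probably small: tenths of a percentage point under moderate assumptions, and 0.5 and 1.0 points with 10% of reads replaced and every in-place read copying SPECT. The effect of the third read runs from nil to +4.3 points on the 95% limit and −7.2 points on the 10% limit, depending on an error correlation that the documents do not give. The documents do not support a claim that the trial is likely to succeed falsely.

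**What to change.** 1. Define the primary MRI and SPECT values as the central blinded second read, and report the consensus result as a secondary analysis. If a consensus value is kept as primary, do not let the in-place read trigger it (for example, adjudicate between two central blinded readers), state that the third reader is blinded to the in-place read and the other modality, and add a sensitivity analysis on the second read alone.
2. Where a scan exists but its blinded read is missing, have it read by another reader in the existing blinded pool, or apply the plan's conservative rule. Use in-place substitution only in a sensitivity analysis.

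The first option costs plan wording and a few reassigned reads; a second central blinded read of each scan would cost more. The required subgroup sizes and the total of 1080 are unchanged. The downside is that the observed proportions may be less favourable to MRI, by an amount that depends on how far readers share errors.

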### Outcome Measures

SPECT and MRI will be compared based on a standardized blinded reader assessment of the imaging methods as well as based on the in-place assessments as part of a workflow incorporated into the clinical routine. To definitely exclude information carry-over in the primary analysis, the following co-primary endpoints are calculated based on the standardized blinded reader assessment:

- The proportion of patients with positive MRI in the group of patients who have a positive SPECT diagnosis for chronic pulmonary embolism and who are positive in the gold standard- The proportion of patients with positive MRI in the group of patients with negative SPECT who are negative in the gold standard.

The co-primary endpoint will also be analyzed based on the in-place assessment and results will be compared to assess the inter-rater agreement and context sensitivity of the diagnostic evaluations and to evaluate the external validity and generalizability of the primary results. Additional secondary endpoints based on the in-place assessment and the blinded-reader assessment include the diagnostic measures sensitivity, specificity, positive and negative predictive values of MRI and SPECT as compared to the defined gold standard. To assess additional benefit of the MRI compared to the SPECT, the proportion of patients with positive MRI in the group of patients who have a negative SPECT, but are positive in the gold standard, and the proportion of patients with negative MRI in patients who are SPECT positive, but have a negative gold standard, will be evaluated.

To assess the safety, the occurrence of allergic reactions or other adverse events, non-completed procedures, reasons for non-completion, non-diagnostic procedures, reasons for non-diagnostic, and the quality of the images will be evaluated for both imaging techniques.

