#### Diagnostic Gold Standard

Catheter pulmonary angiography or computed tomography pulmonary angiography (CPA/CTPA) is considered to be the current clinical gold standard for confirming chronic pulmonary embolism in a diagnostic algorithm (7). CTPA and CPA are well suited as verification step for the diagnosis of chronic pulmonary embolism (18). Nevertheless, they both have a considerable radiation burden on the patient. Therefore, in current diagnostic practice, in many expert centers only patients with a positive SPECT undergo a verification step with CPA/CTPA, whereas at some sites CPA/CTPA is used for verification of all patients. In this study, we only verify patients, if verification with CPA/CTPA is clinical routine at the respective study site. It is the responsibility of the treating pneumologist to decide whether verification by CPA/CTPA is clinically indicated. In any case, verification with CPA/CTPA is not part of study directives but a clinical decision.

A clinical follow-up after 6–12 months is implemented, where all patients are contacted and asked whether there has been any further intervention indicative (or contraindicative) of CTEPH, in order to identify cases diagnosed as false negative (or false positive, respectively) in the diagnostic work-up. Additionally, cases diagnosed as false negative by the screening test (SPECT negative patients are not verified by CPA/CTPA on a regular basis), but subsequently identified as positive can be captured by incorporation of the clinical follow up. Since the gold standard should capture the true diagnosis at inclusion, the clinical follow up diagnosis is restricted to be within 1 year of the inclusion to ensure that CTEPH—if diagnosed in the clinical follow up—was present at the inclusion already and did not develop afterwards.

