### Sample Size

The sample-size calculation was based on a substudy from the Sheffield ASPIRE registry with 132 patients suspected for CTEPH (12). The prevalence of CTEPH was around 60% here, sensitivities and specificities were 96 and 90% for Q-SPECT and 97 and 92% for functional MRI. It was not appropriate to directly utilize these numbers for sample size estimation: First, the primary analysis of the CHANGE-MRI trial uses different, unconventional endpoints due to the incomplete verification by CPA/CTPA. Second, it was unclear, in how far unverified (by CPA/CTPA) patients will occur in the study setting and how large the resulting differential verification bias might be.

Thus, a simulation study was conducted based on the ASPIRE study simulating 1,000 patients in different scenarios. Estimates for the primary endpoint proportions were taken from the mean diagnostic table of 5,000 simulation runs (see Table 2): the proportions of patients with positive MRI within those with positive SPECT and positive gold standard was estimated to be 98% and the proportion of patients with positive MRI within those with negative SPECT and negative gold standard was estimated to be 6%. These estimates were used for sample size calculations with a Chi^2^-test. For both co-primary hypotheses, a one-sided type-I-error of 2.5% and a power of 80% were used. Sample size calculations for the individual hypothesis resulted in 331 patients with positively verified SPECT and 388 patients with negative SPECT and negative gold standard. To calculate the expected overall sample size to achieve this sample sizes for the subgroups, the expected diagnostic table was calculated based on the simulation study. For each hypothesis, the expected overall sample size was calculated taking into account the expected prevalence of each subgroup (58 and 36%, respectively, see Table 2). Consequently, the final sample size was determined by the higher sample size, which is associated with the second primary objective [Table 2, part (b)]. A total of *N* = 1080 required patients are anticipated.

**Table 2 T2:** Sample size calculation based on a simulation study: **(A)** Expected diagnostic table and **(B)** expected required sample sizes for the co-primary endpoints.

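### Where CPA/CTPA follows the in-place SPECT read, in-place and blinded results can differ with equally good readers, and the protocol would read that gap as context sensitivity or limited generalizability

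*Protocol article*

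**What the plan says.** Outcome Measures in the protocol article has the co-primary endpoints analysed on the blinded reads and then again on the in-place reads. The two are compared to judge inter-rater agreement and context sensitivity, and "to evaluate the external validity and generalizability of the primary results". The Discussion gives the in-place reads the same role: "for analyzing the external validity and generalizability of the results based on the primary blinded assessment". Sensitivity, specificity and predictive values of SPECT and MRI are also computed on both sets of reads, against the one defined gold standard.

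Three other statements bear on this:

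- Diagnostic Gold Standard: at many expert centres "only patients with a positive SPECT undergo a verification step with CPA/CTPA", while some sites verify everyone. The treating pneumologist decides, and the study adds no verification.
- In-place Assessment: the SPECT read that belongs to routine care is the local one, "in-place assessment of SPECT (following the clinical routine"). The blinded read is organised centrally and is given no part in the decision to verify.
- The composite gold standard: without CPA/CTPA at work-up, it is the clinical diagnosis at 6–12 months alone.

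The Discussion concedes possible differential verification bias in general terms. It does not say that the bias may act unequally on the two analyses.

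**The concern.** The comparison is meant to isolate reading context: same patients, same images, different readers. At centres that verify only SPECT-positive patients, however, the gold standard itself depends largely on one of the two SPECT reads.

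Take a patient with chronic PE whom the in-place SPECT missed, who had no CPA/CTPA and who was not recognised at follow-up. The gold standard calls this patient negative. In the in-place analysis the patient always counts in the denominator of endpoint 2, usually with a positive MRI. In the blinded analysis that happens only if the blinded SPECT missed the patient as well; otherwise the patient counts as a SPECT false positive. In-place SPECT has some of its misses erased. Blinded SPECT keeps its own misses wherever the in-place read led to verification.

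At stake is what readers of the results are told. MRI could appear to give more false positives in routine use, and local SPECT could appear more accurate than central SPECT, because of verification alone.

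**Working it through.** **Planning figures.** The article states that "a one-sided type-I-error of 2.5% and a power of 80% were used". With n = [z₀.₉₇₅√(p₀q₀) + z₀.₈₀√(p₁q₁)]²/(p₁−p₀)²:

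- Endpoint 1, 95% vs 98%: 330.02, so 331; 331/0.58 = 571.
- Endpoint 2, 10% vs 6%: 387.96, so 388; 388/0.36 = 1078 (stated as 1080).

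These agree with Table 2B. The planned distance between expected value and limit for endpoint 2 is 10 − 6 = 4 points.

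**Table 2A, per 1000 patients.** Endpoint 1 is 562/576 = 97.6% and endpoint 2 is 21/360 = 5.8%. SPECT sensitivity is 576/600 = 96% and specificity 360/400 = 90%, the same as the registry values quoted under Sample Size. The table thus corresponds to every SPECT miss being recognised, and by itself implies no gap.

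**Assumptions, not in the documents.** Both SPECT reads have the Table 2A accuracy, and both MRI reads perform alike. CPA/CTPA is taken as error-free. u is the trial-wide share of in-place SPECT misses neither verified nor recognised at follow-up; sites that verify everyone lower it. r is the chance that the blinded SPECT misses a patient whom the in-place SPECT missed. MRI is positive in 20 of 24 SPECT misses, as in Table 2A.

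**Formulas.**

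- Endpoint 2: in-place (21+20u)/(360+24u); blinded (21+20ur)/(360+24ur).
- SPECT sensitivity: in-place 576/(576+24(1−u)); blinded [576−24u(1−r)]/(576+24(1−u)).
- SPECT specificity: in-place (360+24u)/(400+24u); blinded (360+24ur)/(400+24u).
- Endpoint 1: in-place 562/576; blinded [562−20u(1−r)]/[576−24u(1−r)].

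**Results, in-place vs blinded.**

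| u | r | Endpoint 2 | SPECT sensitivity | SPECT specificity |
|---|---|---|---|---|
| 0 | any | 5.8% vs 5.8% | 96.0% vs 96.0% | 90.0% vs 90.0% |
| 0.2 | 0.75 | 25/364.8 = 6.9% vs 24/363.6 = 6.6% | 96.8% vs 96.6% | 90.1% vs 89.8% |
| 0.2 | 0.5 | 6.9% vs 23/362.4 = 6.3% | 96.8% vs 96.4% | 90.1% vs 89.5% |
| 0.5 | 0.25 | 31/372 = 8.3% vs 23.5/363 = 6.5% | 98.0% vs 96.4% | 90.3% vs 88.1% |
| 1 | 0.5 | 41/384 = 10.7% vs 31/372 = 8.3% | 100% vs 97.9% | 90.6% vs 87.7% |
| 1 | 0.25 | 41/384 = 10.7% vs 26/366 = 7.1% | 100% vs 96.9% | 90.6% vs 86.3% |

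With r=1 the two columns coincide for any u. Endpoint 1 moves by less than half a point even at u=1, r=0.25 (97.6% vs 547/558 = 98.0%).

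**Second model.** A latent-normal simulation calibrated to Table 2A, with equally accurate readers, a correlation of 0.7 between the SPECT reads and only in-place positives verified, gives for endpoint 2:

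- follow-up captures 80% of misses: 6.9% vs 6.2%
- captures 50%: 8.3% vs 6.7%
- captures none: 10.7% vs 7.5%

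If half of the in-place SPECT negatives are verified and follow-up captures 50% of the rest, it is 7.1% vs 6.3%. If everyone is verified, the gap is zero.

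**The case against.** Several counter-arguments have force.

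- **The in-place read does not strictly decide verification.** The pneumologist does, some sites verify everyone, and the 6–12 month follow-up exists to catch SPECT misses. This stands: the gap is possible, not certain. Its size rests on u and r, which the documents do not give. The Sample Size section calls the extent of non-verification and the size of the resulting bias unclear, so u=0 cannot be presumed either.
- **The gap may be small.** Both readers see the same images and clinical information, so r may be high. The article does not say whether the third-reader consensus replaces the blinded read, which could shrink the gap. At u=0.2, r=0.75 it is about 0.25 points, against a 95% half-width of about 2.5 points around 6.5% with n=388.
- **A direct measure of agreement is already planned.** Inter-rater reliability between local and blinded reads is a secondary objective and needs no gold standard. That analysis is unaffected. The article nevertheless also draws conclusions from comparing the endpoint results.
- **Verification bias is disclosed.** It is, but not as something that distorts this comparison.
- **The net direction is not fixed.** The Discussion says independence of the in-place reads cannot be guaranteed. Carry-over from SPECT to in-place MRI could lower in-place endpoint 2. The article also does not say whether the pneumologist sees the MRI result; if a positive MRI prompts CPA/CTPA, u falls.

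A reader might infer that the in-place analysis would fail the 10% limit. The documents set no in-place success criterion. The in-place point estimate reaches 10% only when 21+20u = 36+2.4u, that is u = 15/17.6 = 0.85. The upper Wilson limit passes 10% earlier: at N=1080, u=0.5, r=0.25 it is 11.4% in-place and 9.4% blinded. That is a matter of presentation, not of trial success.

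**Conclusion.** The point holds in conditional form. If some in-place SPECT misses stay unrecognised (u>0) and the two SPECT reads do not always miss the same patients (r<1), endpoint 2 and SPECT sensitivity and specificity differ structurally between the two analyses, even with equally good readers. Over the values tabulated with u above zero, the endpoint 2 gap runs from about 0.25 points to about 3.6 points (41/384 − 26/366), against a planning distance of 4. The upper end needs every in-place miss to remain unrecognised.

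A reader might take this as a flaw in the primary result. The documents do not support that: the success criteria rest on the blinded reads, and neither they nor the sample size use the in-place comparison. What fails is a stated inference in a secondary analysis, which assigns the whole gap to reading context or generalizability.

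**What to change.** Keep the all-in-place proportions as planned, but state that their distance from the blinded results may reflect verification and is not to be attributed to reader or context effects alone. Add two analyses:

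1. **Paired MRI comparison.** Fix the SPECT/gold cells by one SPECT read, for example the final blinded read. Compare in-place with blinded MRI in those same patients and report the paired difference with its interval. This combination of reads does not occur in practice, so it supplements the routine-setting analysis and does not replace it.
2. **Repeat at sites that verify all patients regardless of SPECT result.** Include SPECT sensitivity and specificity there, since verification no longer depends on the in-place read.

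The cost is some analysis-plan wording and a little more analysis on existing data, with no new data collection. Analysis 2 will be less precise because it uses fewer patients.
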